### Statistical analyses

As scores are not independent *within* respondents (repeated measurements) and *between* respondents (three dyads: mother and the adolescent, father and the adolescent, and the parents as partners) multi-level analyses are preferred. However, concerning multilevel models with three levels no agreed upon power analyses are available. Therefore, we estimated study power based on a repeated measurements ANOVA with GPower 3.1.9.7 [30]. We anticipate an effect size of *d* = 0.7 which is based on effect sizes obtained by Attachment-Based Family Therapy, which is akin to EFFT (i.e., *d* = .97 [31] and *d* = 1.08 [32]), and the average effect size we obtained with a Couple relationship Education course based on EFT (i.e., *d* = 0.6 [24]). We computed the required sample size to detect this effect size of *d* = 0.7 with a power of .8 an alpha of .05 and a correction for sphericity of e = .5. It was calculated we would need *n* = 20 families. This is a conservative power-estimation based on the number of families as if we only had one person in each family reporting on the outcome measures. However, as several of our outcomes are dyadic by nature (e.g., outcomes regarding interaction patterns between mother and the adolescent, father and the adolescent, and father and mother as partners) the actual power will be higher as the number of individuals will be twice as high for these outcomes.

Following the power analysis we first plan to run a repeated measurements ANOVA to test our main hypothesis concerning change during treatment plus follow-up on the primary outcome. Subsequently, Linear Mixed Models (LMM) in SPSS will be applied with repeated measurements (level 1) nested within respondents (level 2) and, depending on the specific outcome, respondents nested within the dyad of interest (level 3) [33]. In this way we will be able to assess change over time. An advantage of LMM is the possibility to use cases with partial missing data. To adjust for interdependence of the repeated measurements, the AR1 covariance structure will be applied, and to adjust for interdependence of respondents, we will include an intercept at level 3. When results of the multilevel model converge with the repeated measures ANOVA, trust in the robustness of findings will be enhanced.

We will examine change during the waiting period (comparison of pre-treatment versus pre-waiting period assessments), change during treatment (post-treatment versus pre-treatment assessments), change during follow-up (booster session versus post-treatment assessments), and change during the whole study period (follow-up versus pre-waiting period assessments). We will compute effect sizes (Cohen’s *d*s) using, per comparison, the estimated marginal means, and the pooled standard deviations of the corresponding raw means [34]. Effect sizes will be interpreted as small when Cohen’s *d* is 0.35 or below, moderate when 0.36−0.65, and large when 0.66 or higher. [35]. To evaluate missingness at random, we will apply pattern-mixture models for the dependent variables [36].

The feasibility of EFFT will be evaluated with multiple methods. First, the widely used MAXQDA software will be applied for the qualitative analyses of the semi-structured interviews. We will follow the steps described by Boeije [37]. for inductive thematic analysis. This starts with open coding: fragments relevant to answering the main question will be labeled. Then, several rounds of axial coding will take place where emerging themes within and between participants will be labeled. Finally, the emergent themes will be integrated into an exhaustive representation that describes the overall experience of the families. Second, treatment attendance based upon registrations will be calculated. Finally, treatment adherence will be evaluated by calculating the extent to which the treatment protocol has been executed by the therapists based on ratings by independent raters.

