## Abstract

Mental health issues are widespread among children and adolescents worldwide. Although mental health difficulties may manifest themselves in many different diagnoses, there is growing support for a limited number of underlying transdiagnostic processes. Attachment encompasses a key transdiagnostic mechanism, namely emotional regulation. This study protocol aims to evaluate the feasibility and potential effectiveness of structured emotionally focused family therapy (EFFT), the goal of which is to develop secure attachment between parents and their children to reduce children’s vulnerability to mental health problems. A within-subjects design with three waves, a waiting period, treatment, and follow-up, will be conducted. Families will serve as their own controls. Approximately 15 to 20 families with adolescents (aged 12−18 years) as the ‘identified patients’ will be included. They will participate in 16−21 sessions of EFFT. The study will use a multi-method approach. Self-report questionnaires will be administered repeatedly (i.e., pre-waiting period, pre-treatment, halfway treatment, post-treatment, and follow-up), measuring parent-adolescent attachment, partner-partner attachment, negative interactions, and adolescent psychological complaints. Multi-level analyses will be conducted. Semi-structured interviews will be administered at follow-up to evaluate feasibility and acceptability of EFFT. Treatment integrity will be assessed. The present study is the first to evaluate feasibility of structured EFFT and obtain a first impression of its effectiveness. This information will help us to improve EFFT. Limitations are discussed.

**Trial registration:** Recruitment commenced in June 2022. The approximate trial duration is 36 months. The trial was registered at ClinicalTrials.gov (NCT05657067) on December 9, 2022, and Open Science Framework (https://osf.io/39dt2/) on June 14, 2022.

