### Participants

For this pilot study we will include families with adolescents aged 12−18 years (the so called ‘identified’ patient) who are coping with mild problems. The latter means that we will exclude (a) blended families because of the more complex loyalties that exist between children and stepparents, (b) families of which individual members cope with serious trauma such as sexual and physical abuse and severe neglect, and (c) families of which the parents or children are diagnosed with severe DSM disorders (substance abuse or psychosis) or are in therapy to maintain sufficient research sample homogeneity for this pilot study. Exclusion criteria will be determined with unstructured clinical interviews by experienced clinicians during the screening. Families will be recruited by five private EFFT practices in the Netherlands. Prior to entering the study participants are asked to give their informed consent, whereas parents provide consent for their children under the age of 16. For this pilot study we aim for 15−20 included families who will be treated by five family therapists supervised by one International Centre for Excellence in Emotionally Focused Therapy (ICEEFT) certified psychotherapist. The study was approved by the Ethics Review Board of the University of Amsterdam (2022-CP-15102) on June 10, 2022. The trial is registered at ClinicalTrials.gov (NCT05657067) on December 9, 2022, and Open Science Framework (https://osf.io/39dt2/) on June 14, 2022 and will be conducted from June 2022 onward.

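### The power calculation requires 20 families, but 15–20 are planned with no attrition allowance, so power of 0.8 is reached only at the top of the range

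*Protocol article*

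**What the plan says.** The Statistical analyses section of the protocol article bases power on a repeated measures ANOVA in GPower. The effect size is given as "We anticipate an effect size of *d* = 0.7 which is based on effect sizes obtained by Attachment-Based Family Therapy", together with an effect from a couples course. The other stated inputs are "with a power of .8 an alpha of .05 and a correction for sphericity of e = .5". The result is "It was calculated we would need *n* = 20 families".

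Two comments on that result follow. The first is "This is a conservative power-estimation based on the number of families as if we only had one person in each family". The second is that, for dyadic outcomes, "the actual power will be higher as the number of individuals will be twice as high for these outcomes".

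The recruitment target appears elsewhere. The Abstract has "Approximately 15 to 20 families with adolescents", and Participants has "we aim for 15−20 included families who will be treated by five family therapists".

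No allowance for attrition is given. Procedure and assessments instead describes on-site questionnaire completion, intended to make full response likely from the second assessment on. The first planned test of the main hypothesis is the repeated measures ANOVA over treatment plus follow-up. A linear mixed model (LMM) comes after it, and the article credits the LMM with being able to use partly missing cases.

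**The concern.** The required number is the upper limit of the planned number. A study that ends with 15, 16 or 18 families will have met its recruitment target and still fall short of the power the article reports. So will a study that recruits 20 and loses one. The comments that the estimate is conservative and that actual power will be higher invite the reader to disregard this gap, but the article gives no figure showing that they close it.

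What is at stake is how a null or borderline result is read. If the primary ANOVA is not significant with 15 or 16 families, a reader who relies on the power paragraph will take it as the outcome of a test with power 0.8 or better for d = 0.7. On the reconstructed inputs, the chance of missing that effect would be about 0.30 to 0.33.

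**Working it through.** **Inputs**
- Stated in Statistical analyses: d = 0.7, alpha 0.05, target power 0.80, sphericity correction e = 0.5, required n = 20.
- Stated in Abstract and Participants: 15–20 families planned.
- Not stated, so assumed: f = d/2 = 0.35; m = 4 occasions (treatment plus follow-up read as t2 to t5); correlation between occasions r = 0.5.

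**Formula** (one group, within-subject factor, noncentral F)
- λ = n·m·f²·e/(1 − r)
- df1 = (m − 1)·e
- df2 = (n − 1)(m − 1)·e

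**Step 1: reproduce the article's figure.** For n = 20:
- λ = 20 × 4 × 0.1225 × 0.5/0.5 = 9.80
- df1 = 3 × 0.5 = 1.5
- df2 = 19 × 3 × 0.5 = 28.5
- Power = 0.805

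At n = 19 power is 0.782, so 20 is the smallest n that reaches 0.80. This matches the article exactly. With the other inputs unchanged, m = 5 gives n = 18 and m = 3 gives n = 24.

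**Step 2: power across the planned range, same inputs.** For n = 15, λ = 15 × 4 × 0.1225 × 0.5/0.5 = 7.35, df1 = 1.5 and df2 = 21.

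| Complete families | Power, m = 4 | Power, m = 5 |
|---|---|---|
| 20 | 0.805 | 0.863 |
| 18 | 0.757 | 0.819 |
| 16 | 0.698 | 0.764 |
| 15 | 0.666 | 0.731 |

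**Step 3: attrition.** These are complete families, because a repeated measures ANOVA ordinarily drops a case with a missing occasion. To finish with 20 complete families, recruitment would have to be 20/0.9 = 22.2, so 23, at 10% loss, or 20/0.8 = 25 at 20% loss. Both loss rates are assumptions. Either number lies above the planned range.

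**Step 4: sensitivity to the unstated inputs.**
- Correlation, at m = 4 and f = 0.35: r = 0.3 needs 27 families and gives power 0.52 at 15; r = 0.7 needs 13 and gives 0.88 at 15.
- Time course. If d = 0.7 is the span of the means and gain is gradual over t2 to t5 (0, 0.35, 0.7, 0.7), the mean is 0.4375 and f is the standard deviation of the four means, 0.290. At r = 0.5 and e = 0.5, power is 0.64 at 20 families and 0.50 at 15.
- Adding a flat waiting period (0, 0, 0.35, 0.7, 0.7; m = 5) gives f = 0.313, with power 0.77 at 20 and 0.63 at 15.

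**Step 5: what a second report per dyad adds.** With correlation r_d between the two reports, the effective number is 2n/(1 + r_d). Here r_d is assumed.
- 20 families: 40/1.4 = 28.6 at r_d = 0.4, and 40/1.7 = 23.5 at r_d = 0.7.
- 15 families: 30/1.4 = 21.4 at r_d = 0.4, and 30/1.7 = 17.6 at r_d = 0.7.

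This is a gain, but less than a doubling.

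**The case against.** **The calculation contains cautious choices.** The sphericity correction of 0.5 is severe: under an AR1 pattern over four occasions, epsilon would be 0.86 at correlation 0.5 and 0.77 at 0.7. With e = 0.8 and f = 0.35, 15 families would suffice, and the gradual course would give 0.79 at 20. The assumed d = 0.7 is below both cited family-therapy effects (0.97 and 1.08). Only one reporter per family is counted. All of this stands, and it rules out calling 0.8 a ceiling.

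**A reader might infer that the calculation relied on the most favourable possible time course.** For four means spanning 0.7, f = 0.35 is indeed the largest attainable value. But the conversion, the occasions and the correlation are not in the article, and other inputs also lead to about 20. The gradual course over t2 to t5 needs 21 families at r = 0.65 and 18 at r = 0.7. The five-occasion course needs 22 at r = 0.5 and 18 at r = 0.6. So the documents support neither that inference nor the label best case.

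**A reader might also infer that the article counts dyad members as independent.** It does not say so. It says that power will be higher, which is right in direction for the LMM, and the same section recognises the dependence and models it with a level-3 intercept. What remains is that the size of the gain is not given, and that nothing shows whether it reaches the ANOVA planned first.

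**This is a pilot.** It seeks an initial indication of effectiveness, acknowledges its limited size and foresees a larger controlled study. Response is collected on site, and the LMM tolerates partial data. These points lower the severity. They do not reconcile 20 required with 15–20 planned.

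**Conclusion.** The mismatch holds and can be read directly from the article: the required number is the top of the planned range, and no loss is allowed for. On the inputs that reproduce n = 20, power runs from 0.67 at 15 complete families to 0.81 at 20. If five occasions were used, the lower end is 0.73, and 0.80 is reached from 18 families.

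These figures rest on f = 0.35, r = 0.5 and m = 4, all inferred, and on complete families being the unit of the ANOVA. At exactly 20 complete families the stated power holds. The gradual-gain figures (0.50–0.64) are a scenario under the same r and e, not a demonstrated error. The word conservative is justified for counting one reporter per family. It is not shown for the calculation as a whole.

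Severity: should be corrected, but below a must-fix for a pilot.

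**What to change.** In Statistical analyses:
1. Replace the single requirement with a range: about 0.67–0.80 power for 15–20 complete families at d = 0.7. Revise it if the authors' actual inputs differ from those inferred here.
2. State the number of occasions, the correlation and the d-to-f conversion entered in GPower, and say that no attrition is allowed for or what allowance is made.
3. Add a sensitivity note: under r = 0.5 and e = 0.5, gradual gain over t2 to t5 (f = 0.29) gives about 0.50–0.64. Label it a scenario.
4. Limit the word conservative to the one-reporter-per-family point.
5. Replace the doubling remark with the statement that a second report per dyad raises the effective number to 2n/(1 + r), with r assumed, and that this applies to the LMM on dyadic outcomes.

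Cost: a few sentences and a less favourable power figure. No extra families and no change of design or analysis.

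### The main-hypothesis test is given to a repeated-measures ANOVA, which by default drops incomplete cases; the mixed model comes second and no rule covers disagreement

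*Protocol article*

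**What the plan says.** All of the following is in the protocol article.

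- **Main test.** Statistical analyses: "we first plan to run a repeated measurements ANOVA to test our main hypothesis concerning change during treatment plus follow-up on the primary outcome". The only reason given is that this follows the power analysis.
- **Stated preference.** The same section opens by saying that, because scores are dependent within and between respondents, "multi-level analyses are preferred".
- **Mixed model.** It is applied after the ANOVA, with an AR1 structure for the repeated measurements and an intercept at dyad level. The section notes: "An advantage of LMM is the possibility to use cases with partial missing data".
- **Relation between the two.** "When results of the multilevel model converge with the repeated measures ANOVA, trust in the robustness of findings will be enhanced". Disagreement is not addressed.
- **Sample size.** "We anticipate an effect size of *d* = 0.7", "with a power of .8 an alpha of .05 and a correction for sphericity of e = .5", and "It was calculated we would need *n* = 20 families". The abstract plans about 15 to 20 families. No dropout rate or allowance is given.
- **Data collection.** Procedure and assessments: after the pre-waiting assessment, respondents fill in the forms in the therapist's room shortly before a session. The aim is to make full response probable.
- **Missing data.** Later in Statistical analyses, pattern-mixture models are planned for the dependent variables to examine missingness at random. They are not attached to either analysis.

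**The concern.** The section argues for one method and gives the main test to another. A standard repeated-measures ANOVA needs a score at every occasion it includes. If treatment plus follow-up means t2 to t5, a unit that supplies t2 and t3 and then stops contributes nothing, and a unit that misses only t5 is lost entirely.

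Collecting forms on site guards against forgotten questionnaires, but it ties t2 to t5 to attendance. A family that leaves treatment has no described route to t4 or t5, so the missing data that remain are likely to be related to treatment. If families who gain little by t3 are more likely to leave, those who stay show more change than those who started.

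At stake are a main test that may lean in favour of the intervention, a loss of power in a study of 15 to 20 families, and a choice between two results that could be made after both are seen.

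**Working it through.** **1. Reproducing the sample size.** Inputs from Statistical analyses: d = 0.7, power 0.80, alpha 0.05, sphericity correction ε = 0.5. Assumptions: f = d/2 = 0.35; m = 4 assessments (t2 to t5); correlation ρ = 0.5, which is not stated.

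For a one-group within-subject F test:
- λ = N·m·f²·ε/(1−ρ)
- df1 = (m−1)·ε
- df2 = (N−1)·(m−1)·ε

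With N = 20:
- λ = 20 × 4 × 0.1225 × 0.5/0.5 = 9.8
- df1 = 3 × 0.5 = 1.5
- df2 = 19 × 1.5 = 28.5
- power = 0.805, and 20 is the smallest N that reaches 0.80.

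The stated 20 is reproduced, for 20 families with complete data. It is sensitive to what is unstated: with m = 4, ρ = 0.3 gives 27 and ρ = 0.7 gives 13; with ρ = 0.5, m = 3 gives 24 and m = 5 gives 18.

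**2. Power when incomplete families are dropped** (m = 4, ρ = 0.5; loss rates assumed)

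| Enrolled | Loss | Complete | Power |
|---|---|---|---|
| 20 | 0% | 20 | 0.805 |
| 20 | 10% | 18 | 0.757 |
| 20 | 20% | 16 | 0.698 |
| 20 | 30% | 14 | 0.630 |
| 15 | 0% | 15 | 0.666 |
| 15 | 20% | 12 | 0.551 |

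For 16 complete families, λ = 16 × 4 × 0.1225 = 7.84 and df2 = 15 × 1.5 = 22.5. These figures follow the protocol's own basis of one reporter per family. The drop from 0.805 to 0.666 between 20 and 15 complete families comes from enrolment, not from the choice of method.

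**3. Bias when leaving depends on observed early change.** Scores at t2 to t5 were simulated with unit SD, correlation 0.5 and mean changes from t2 of 0, −0.35, −0.70 and −0.70 (lower is better). Dropout after t3 was logistic in the t2-to-t3 change, with slope 1 per SD. Each setting used 4,000 simulated units so that bias, not noise, is seen.

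| Dropout | Completers, t2 to t4 | Full sample | Likelihood, all observed data | Completer overstatement |
|---|---|---|---|---|
| about 10% | −0.722 | −0.672 | −0.678 | 0.050 |
| about 20% | −0.762 | −0.682 | −0.675 | 0.080 |
| about 30% | −0.824 | −0.692 | −0.698 | 0.132 |

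**4. How far the size depends on the assumptions.** With 20 families, a true gain of 0.70 SD and correlations of 0.3 to 0.7, the completer gain was:
- weak dependence, 10% dropout: 0.72-0.74
- moderate dependence, 25% dropout: 0.80-0.84
- strong dependence, 25% dropout: 0.86-0.91

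The overstatement therefore runs from 0.72 − 0.70 = 0.02 to 0.91 − 0.70 = 0.21 SD. The likelihood estimate stayed at 0.69-0.71.

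**5. When leaving depends on unobserved scores.** With dropout driven by the t2-to-t4 change, where t4 is missing for those who leave, the likelihood estimate was also too high: 0.86-1.00 against 0.70.

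**The case against.** The strongest defence is that the plan already contains the better analysis. The mixed model is planned, the section says it is preferred, the abstract names only multi-level analyses, and pattern-mixture models are foreseen. Effect sizes are to be computed from estimated marginal means in a paragraph that follows the mixed-model description, so they plausibly come from that model, although the text does not say so.

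A reader might therefore infer too much in several ways:

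- **That the trial's headline result will be completer-only.** The documents do not support this. The ANOVA is given a hypothesis test, and the reported size of change may well rest on all available data. Deletion of incomplete units is also the method's default, not protocol text; the unit of analysis and the included occasions are not spelled out.
- **That the gain would be overstated by about a quarter (0.89 against 0.71 SD).** This needs about 25% dropout with strong dependence on early change. The documents support neither the rate nor the premise that non-improvers leave.
- **That a small rate of missed forms would remove nearly half the families.** With 5% missed per form, 0.95^12 = 0.54 are complete only if a family score needs three members at four occasions. No such score is planned, and on-site completion makes scattered missing forms less likely.
- **That agreement between the two analyses would be nearly automatic without dropout.** This is not shown. The mixed model adds AR1 errors and a dyad intercept, so the comparison also checks modelling assumptions.
- **That the mixed model removes the bias.** It does so only if leaving depends on observed scores. The protocol's AR1 structure can also misfit: with about 25% dropout and a true gain of 0.70 SD, an AR1 fit gave about 0.65-0.68.

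What remains is the precedence. The order of the two analyses is fixed in the text, the reason given is only that the power calculation used the ANOVA, and disagreement is not covered. On-site completion does not reach families who stop, and the pattern-mixture models are not tied to the main test.

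**Conclusion.** The point holds as a matter of which analysis carries the main test and what happens if the two disagree. Under assumed dropout of 10-25% that depends on observed early change, the ANOVA would be too favourable by roughly 0.02 to 0.2 SD. The direction is consistent under that assumption; the size is not firm, because the protocol gives no dropout rate. With full response there is no bias and no loss. At an assumed correlation of 0.5, power falls from about 0.80 with 20 complete families to about 0.70 with 16. The mixed model is the better main test because it uses the early scores of families who leave, but it still rests on missingness at random.

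**What to change.** In Statistical analyses:

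1. Name the linear mixed model, fitted to all available assessments from every enrolled family including those who stop, as the test of the main hypothesis on the primary outcome.
2. Keep the repeated-measures ANOVA, labelled as a complete-case sensitivity analysis.
3. Extend the convergence sentence: if the two differ, the mixed-model result stands and the difference is reported.
4. Attach the pattern-mixture models to the mixed model as the check on its missing-at-random assumption.

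All these analyses are already planned, so the change is one of wording and needs no new data. The cost is that the ANOVA-based power figure becomes an approximation for the main test, and the text should say so.

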The current pilot study is designed as a first test of the newly developed protocol of structured EFFT. Therefore, it is important to evaluate whether such treatment is desirable and feasible, and establish an initial indication of its effectiveness. Evaluation of the feasibility of EFFT will be based on semi-structured interviews with family members who participated in order to obtain their evaluation of (specific phases of) EFFT and to identify possible points of improvement of EFFT. Concerning the effectiveness of EFFT, only one early pilot study is available that has shown EFFT to be a promising intervention for families with children suffering from bulimia [19]. However, we expect EFFT to be effective since emotionally focused couples therapy (EFCT), of which EFFT is a fundamental extension, is an empirically supported treatment [20]. In this study we will examine the effectiveness of structured EFFT with regard to several outcomes. We chose escalation in negative interactions between child, mother and father as the primary outcome measure as the transdiagnostic idea that the child’s problems are originating in and/or exacerbated by negative interactions within the family is central to EFFT. Other equally important outcome measures are accessibility and responsiveness of the parents to the child’s and their partner’s needs, attachment between the parents and the child, and child psychological complaints. Additional outcome measures are: disciplining of the child by the parents; attachment between the parents as partners, and parental relationship satisfaction. Concerning all outcomes, we hypothesize:

less change during the waiting period compared with the treatment phase;gain during the treatment phase; andsubstantial maintenance during follow-up.

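### The repeated-measures ANOVA named for the main hypothesis appears to be a directionless time F-test, which alone cannot separate gain and maintenance from relapse, worsening or follow-up-only change

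*Protocol article*

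**What the plan says.** All places are in the protocol article.

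- **Introduction, hypotheses.** Three statements cover all outcomes: "less change during the waiting period compared with the treatment phase", "gain during the treatment phase", and gains largely kept over follow-up. The second and third are directional and each belongs to a phase.
- **Statistical analyses, sample size.** "we estimated study power based on a repeated measurements ANOVA with GPower 3.1.9.7". "We anticipate an effect size of *d* = 0.7", "with a power of .8 an alpha of .05 and a correction for sphericity of e = .5". The result is 20 families.
- **Statistical analyses, main test.** "we first plan to run a repeated measurements ANOVA to test our main hypothesis concerning change during treatment plus follow-up on the primary outcome". No contrast, direction or decision rule is attached. Linear mixed models follow, and agreement between the two analyses is to raise confidence in the findings.
- **Statistical analyses, comparisons.** The plan will examine waiting period (t2 v t1), treatment, follow-up (t5 v t4) and whole-study (t5 v t1) change, each with a Cohen's d. The treatment comparison is worded "change during treatment (post-treatment versus pre-treatment assessments". These comparisons are not named as the test of the main hypothesis.

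**The concern.** The time F-test in a repeated-measures ANOVA has the null that all occasion means are equal. Any departure counts against that null: improvement or deterioration, during treatment or after it, lasting or lost. The hypotheses to be tested are narrower: scores improve from t2 to t4, and the improvement is still there at t5. A significant F is compatible with both of these being false.

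Two things are at stake. The first is what a significant result on the named test may be taken to show. The second is the robustness argument: if the ANOVA is directionless, its agreement with the multilevel model says little about whether families gained.

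**Working it through.** **Step 1. Which test was sized?**

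Inputs from Statistical analyses: d = 0.7, alpha 0.05, power 0.80, epsilon 0.5. Assumed: f = d/2 = 0.35 and a correlation ρ of 0.5 between occasions, since the article does not give one. For m occasions and n families:

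- λ = f²·n·m·ε/(1−ρ)
- df1 = (m−1)·ε
- df2 = (n−1)·(m−1)·ε

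With m = 4 (t2 to t5, which fits treatment plus follow-up) and n = 20:

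- λ = 0.1225 × 20 × 4 × 0.5/0.5 = 9.8
- df1 = 3 × 0.5 = 1.5
- df2 = 19 × 3 × 0.5 = 28.5
- power = 0.805, and 20 is the smallest n that reaches 0.80

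This is the article's figure. At ρ = 0.5, three occasions give 24 families, five give 18 and six give 16. With four occasions, ρ of 0 / 0.3 / 0.6 / 0.7 gives 38 / 27 / 17 / 13. The match is not unique (three occasions with ρ = 0.6 also give 20). A sphericity correction matters only for a within-subject F with more than one degree of freedom, so the sized test is a time F of that kind.

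**Step 2. What does that F reject?**

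Simulation: 20,000 trials per pattern, n = 20, SD 1, one score per family, Greenhouse-Geisser corrected F on t2 to t5. Scores are coded so that positive means improvement. The t4−t2 contrast is a paired t counted only when significant at 0.025 in the direction of improvement. Entries are for compound symmetry 0.5, then AR(1) 0.7; both correlation structures are assumptions.

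| True means t2, t3, t4, t5 | Time F | Directed t4−t2 |
|---|---|---|
| Gain kept (0, .35, .7, .7) | 0.838 / 0.793 | 0.844 / 0.837 |
| Full relapse (0, .35, .7, 0) | 0.836 / 0.894 | 0.845 / 0.830 |
| Worsening (0, −.35, −.7, −.7) | 0.834 / 0.791 | 0.000 / 0.000 |
| Follow-up only (0, 0, 0, .7) | 0.872 / 0.870 | 0.024 / 0.023 |
| No change | 0.043 / 0.046 | 0.025 / 0.025 |

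The F holds its level when nothing changes, but rejects at much the same rate for the hypothesised pattern and for the three contrary ones. Worsening is the mirror image of gain, so those two rates are equal apart from simulation error.

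**Step 3. Does the number of occasions matter?**

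- Five occasions, compound symmetry: gain kept 0.935, waiting-period change only 0.857, relapse 0.857, worsening 0.931.
- Five occasions, AR(1): 0.822, 0.789, 0.827, 0.819 in the same order.
- Three occasions, compound symmetry: gain kept 0.871, relapse 0.874, worsening 0.870, follow-up only 0.875.

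The conclusion survives each reading. It is less stark with five occasions under compound symmetry.

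**Step 4. What would matched contrasts do?**

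For t4−t2 under compound symmetry, the SD of the difference is √(2 × (1−0.5)) = 1, so dz = 0.7. Power is 0.713 at n = 15 and 0.844 at n = 20, and 19 families suffice for 0.80. Under AR(1) 0.7 the t2–t4 correlation is 0.49, the SD is √(2 × 0.51) = 1.01, and power is about 0.70 and 0.84.

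The table shows that t4−t2 alone still rejects under full relapse. A single average of t4 and t5 minus t2 does not solve this: at n = 20 it rejects about 30–41% of the time under relapse or under follow-up-only change. Requiring directed t4−t2 and t5−t2 together rejects about 2.4% under relapse and 0% under worsening. Under gain kept, its power is about 69–75% at n = 20 and 53–57% at n = 15.

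**The case against.** The strongest reply is that the contrasts are already planned. Treatment change and follow-up change are both listed with effect sizes that carry a sign, so a relapse would appear as a t5−t4 change and worsening as a reversed sign. An overall F followed by planned comparisons is an ordinary sequence, and the article states a preference for multilevel analyses. This stands, and it limits the harm. It does not remove it, because those comparisons are not named as the test of the main hypothesis and the ANOVA's conclusion is not made to depend on them.

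It is also true that the article never calls the ANOVA an overall test and does not say which occasions enter it. That reading rests on the power calculation.

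Three stronger readings are tempting, and the document does not support them:

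- **A significant F will be reported as gain.** Nowhere does the article say so. The Discussion bases attribution on treatment change exceeding waiting-period change.
- **The type I error is inflated.** A reader might set the 87% for follow-up-only change against 5%. In that pattern the means do differ, so the F is right to reject its own null; the 5% belongs to a different test.
- **The F costs much power.** At n = 20 it has 84% against 84% for t4−t2 under compound symmetry, and 79% against about 84% under AR(1). A larger loss appears only if epsilon is fixed at 0.5 in the analysis, and the article uses that value only for sample size.

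**Conclusion.** The point holds in a limited form. The test named for the main hypothesis appears to be a directionless time F. At n = 20 with a 0.7 SD change it rejects 79–89% of the time under full relapse, worsening or follow-up-only change, against 79–84% under the hypothesised pattern. It cannot by itself support gain and maintenance, and its agreement with the multilevel model adds little support for gain.

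The evaluation as a whole is not undermined, since the planned phase comparisons give direction and timing. The case for change rests on interpretation, not on error rates or power. The figures assume four occasions, one score per family, and correlations of 0.5 (compound symmetry) or 0.7 (AR(1)), none of which the article states for this test. In an uncontrolled pilot seeking a first impression of effectiveness, this is a correction worth making, not a fatal flaw.

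**What to change.** In Statistical analyses:

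1. Name the already planned t4−t2 contrast on the primary outcome, with its sign and 95% CI, as the test of treatment gain.
2. Add t5−t2, with sign and 95% CI, as the test that gain remains at follow-up. The t5−t4 comparison stays as a description of what is lost. The article gives no margin for maintenance, so t5−t2 shows that some gain remains, not that all of it does.
3. Claim gain that is maintained only if both contrasts show improvement.
4. Keep the time F as descriptive, and rest the convergence argument on the contrasts.
5. Restate the power sentence for d = 0.7 with its assumed correlation. At n = 20, t4−t2 alone has about 83–84% and both contrasts about 69–75%. At n = 15, the lower end of the recruitment range, the figures are about 70–71% and 53–57%.

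The cost is wording and a recomputed power figure; no new data or families are needed for the gain contrast. The downside is that the joint claim falls below 80% power even at 20 families, and that t4−t2 is less sensitive to a slow gain completed only at t5. For a straight-line gain reaching 0.7 SD at t5 (0, .23, .47, .7), its power at n = 20 is about 51%.
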